#### Secondary analyses

The secondary outcome is the nursing home residents’ quality of life, which will be assessed at t_0_, t_1_ and t_2_ with the EQ-5D-5L [34, 35]. The analyses will also use a generalised linear mixed-effect regression model with EQ-5D-5L score changes over 1 year as the dependent variable, adjusted by the baseline value. Each nursing home will be given a random intercept.

The analyses of the primary and secondary outcomes will also allow for an additional adjustment for cluster and individual-specific confounding baseline variables such as age, gender, length of stay and grade of care at the individual level as well as ownership, number of residents, staff mix and ratio, and use of strategies for dealing with joint contractures or participation restrictions.

#### Further statistical issues

At each time point, if DSS ≥ 3, the outcome measurements will require a proxy rating. Sensitivity will be ascertained by removing these proxy ratings from the analysis. To investigate the impact of other influencing factors on the effect of PECAN, different subgroup analyses might be done. The necessity and feasibility of different subgroup analyses will be considered. The impact of missing values will be done by comparing complete case analyses with multiple imputation analyses.

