#### Blinding

Due to the characteristics of the intervention, it is not possible to blind the nursing staff, the nursing home residents or the researchers involved in delivering the intervention to the group allocation. However, the researchers and study assistants who collect the data at the different times and the biostatisticians who perform the data analysis will be blinded.

If an outcome assessor becomes unblinded, they will no longer collect data but will be replaced with another trained, blinded researcher. To estimate the success of blinding, the outcome assessors will be formally asked to guess the allocation of the study groups including a justification ; their responses will be compared with what would be expected by chance [21]. If data indicates that blinding was unsuccessful, we will replace the outcome assessor with another blinded researcher. 

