### Outcome measures

Data for outcomes and other variables will be collected at three measurement points: at baseline before randomisation (t_0_), after 6 months (t_1_), and after 12 months (t_2_). Table 1 provides an overview of the different variables on an individual level, which includes the ratings of the nursing home residents. We will assess the cognitive status of the residents at each time point to decide if the outcome measurements will require a proxy rating, which the nursing staff will perform.

**Table 1 Tab1:** Instruments and measures at resident level

Instrument	Outcome	Measurement point		
		t_0_	t_1_	t_2_
Primary outcomes				
PaArticular Scales, subscale participation [17]	Participation	X	X	X
PaArticular Scales, subscale activities [17]	Activities	X	X	X
Secondary outcomes				
EQ-5D-5L [34, 35]	Health-related quality of life	X	X	X
Additional data sources				
Medical records	Clinical data	X	X	X
DSS [36]	Cognitive impairment	X	X	X
CMAI [37, 38]	Behavioural symptoms	X	X	X
Clinical records	Falls and fall-related consequences	X	X	X
Clinical records	Physical restraints	X	X	X

*CMAI* Cohen–Mansfield Agitation Inventory, *DSS* Dementia Screening Scale, *EQ-5D-5L* EuroQol Five-Dimension Five-Level Instrument, *t*_*0*_ baseline before randomisation, *t*_*1*_ 6 months post-randomisation, *t*_*2*_ 12 months post-randomisation

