For each subscale, the nursing home resident or, if not possible, a proxy (nurse), assesses their existing difficulties for the different items on a scale ranging from 0 for “no problem”, 1 for “mild to moderate problem” and 2 for “severe problem” to 3 for “complete problem”. Additionally, an item is assigned “C” if the difficulty can be assigned without doubt to a cause other than the contracture. For both the participation subscale and the activity subscale, the scores are summed to give an initial ordinal raw score. This is transformed into an interval scaled score, ranging from 0 to 100, to allow comparisons at the interval level.

A mean decrease of ten points on the participation or activity subscale of the PaArticular Scales at t_2_ is considered as a clinically meaningful difference in favour of the PECAN intervention. This would represent a change from “complete problem” to “mild/moderate/severe problem” or from “mild/moderate/severe problem” to “no problem” in one of the patient-relevant items. The ten-point difference is also in line with the suggested distribution-based methods for defining a minimally important difference as at least 1/2 of the standard deviation [43], because the standard deviation in the baseline data from our pilot study is about 14, which is below 20.

In a recent review of the test–retest reliability of patient-centred self-reported measures for older people, the methodological quality of the PaArticular Scales was assessed as “fair” [44].

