#### Additional measures

We will collect further data for descriptive purposes (see Table 1). On an individual level, we will collect clinical data such as length of stay at baseline. In addition, we will collect grade of care, urinary and faecal incontinence, affected joints, provision of adaptive technologies, medical aids, physical therapy and occupational therapy at each time point. Additional characteristics will be collected from nurses’ assessments of the residents’ cognitive status and behavioural symptoms that are related to dementia.

A nurse will rate the cognitive status of each resident during the last month of the intervention using the Dementia Screening Scale (DSS) [36] to assess whether a proxy rating is required. The DSS contains the dimensions memory and orientation, giving a total of seven items each with a three-point scale (never, occasionally or always). The tallied responses result in an overall score with a range from 0 to 14, higher values indicating a greater degree of cognitive impairment. A proxy rating is performed at a cut-off point of 3.

The residents’ behavioural symptoms will be determined using a modified German version [45] of the Cohen–Mansfield Agitation Inventory (CMAI) [37, 38], as used in previous studies [46, 47]. The inventory consists of five symptom complexes: restlessness, verbal agitation, handling things inappropriately, negative attitude and aggression. Each complex is rated on a four-point Likert scale (never, once or twice, repeatedly, permanently) that assesses symptoms within the preceding four weeks.

On a cluster level, we will record the ownership of the nursing home (public, non-profit-organisation or private), its location and surroundings, the number of residents, the number and size of wards, the number of residents with joint contractures, staff mix and ratio, and the use of strategies for dealing with joint contractures or participation restrictions by interviewing the director of the nursing homes or head nurse at baseline.

To document adverse events that are potentially associated with the PECAN intervention, we will collect data on an individual level concerning the incidence of falls, fall-related consequences as well as the number and types of physical restraints used.

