#### Data collection and management

All assessments will be performed on a paper-and-pencil basis by blinded members of the research team, who will be thoroughly trained in the data collection procedure.

Only pseudonymised data will be collected at the study centres in Halle (Saale) and Rosenheim, i.e. no personal data about the participants will be recorded or saved. The participating nursing homes will be allocated a pseudonymised number. To compare the outcomes from the measurement points, each participant will be assigned a code from a list, which will be stored separately and can be accessed only by the researchers at the study centres. The list will never be merged with the pseudonymised data and will be destroyed after the final validation of the analysis data set.

After each measurement point, the paper-based pseudonymised data at resident level from the study centres in Halle (Saale) and Rosenheim will be transferred to the biostatisticians’ institution, where the data entry and analysis will be performed by the data managers and biostatisticians. A copy of the questionnaires will remain safely stored at the respective study centres.

All answer to the questionnaires will be entered into a database and validated through double entry. The first data entry will take place at the latest 1 month after the different time points. Additionally, the data will be checked for inconsistency and completeness and its quality will be reported to the study centres.

The pseudonymised data will be stored on a secure computer. These data will be handled in accordance with the data protection declaration of the biometric institution. The server and all connected data arrays are in a limited access server room that is protected by a key card system and an alarm. The data will be encrypted and password-protected when being transferred between secure servers. Any hard-copy printouts, USB data versions or other removable media that are used to transfer protected health information will be destroyed after the transmission is complete.

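### The only stated check on unblinded nurse proxy ratings selects residents by a post-randomisation nurse score, so a baseline-defined analysis should be added beside it

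*Protocol article*

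**What the plan says.** Under Further statistical issues the proxy rule is applied visit by visit: "At each time point, if DSS ≥ 3, the outcome measurements will require a proxy rating". The Outcome measures section says that cognitive status is assessed at each time point "to decide if the outcome measurements will require a proxy rating, which the nursing staff will perform". The Primary outcome section confirms that this covers both PaArticular subscales: "For each subscale, the nursing home resident or, if not possible, a proxy (nurse), assesses their existing difficulties".

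The Blinding section states that "it is not possible to blind the nursing staff, the nursing home residents or the researchers involved in delivering the intervention". Only the data collectors and the biostatisticians are described as blinded, and the allocation-guess exercise is put to the outcome assessors. The Data collection and management section says: "All assessments will be performed on a paper-and-pencil basis by blinded members of the research team".

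The DSS is itself a nurse rating. Additional measures says: "A nurse will rate the cognitive status of each resident during the last month of the intervention". Table 1 also lists it at t0, t1 and t2, and t0 falls before randomisation.

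The stated check on proxy ratings is: "Sensitivity will be ascertained by removing these proxy ratings from the analysis". The other stated sensitivity analysis, complete cases against multiple imputation, concerns missing values.

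**The concern.** PECAN works through nurses. The Implementation strategy section says that it aims to change their professional attitudes and behaviour. The same group, knowing the allocation, scores the primary outcome for cognitively impaired residents. If nurses in PECAN homes come to rate participation or activities more favourably without a real change in the resident, the arm difference moves towards benefit. The protocol describes the population as one in cognitive decline, so the proxy group is unlikely to be marginal.

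The deletion analysis is the safeguard against this, but its membership rule uses the DSS at each visit, scored at t1 and t2 by unblinded staff. The retained residents are therefore no longer the groups formed by randomisation. The check also moves to a different population, residents who are still cognitively intact at follow-up. A result that differs from the main analysis would have at least three explanations, and the planned analyses would not distinguish them.

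**Working it through.** **1. The plan's own figure.** Inputs from Sample size calculation: difference 10, variance 200, two-sided alpha 0.025 per subscale, power 80%, ICC 0.38, 15 residents per home.

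- Per arm before inflation: 2 × 200 × (2.241 + 0.842)² / 10² = 38.0.
- Inflation factor: 1 + 14 × 0.38 = 6.32.
- 38 × 6.32 = 240.2, against the stated 241. The figure reproduces and is not in dispute.
- Implied standard error of the arm difference: √(2 × 200 × 6.32 / 241) = 3.24. Power for 10 points is 80.1% (normal approximation).

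**2. Rater bias in the primary analysis.** The protocol gives neither the proxy share p nor any rating shift b, so both are assumed. If intervention-arm proxies rate b points more favourably on average, the arm difference is biased by p × b. With no true effect, the two-sided rejection probability is Φ(pb/3.24 − 2.241) + Φ(−pb/3.24 − 2.241).

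| Assumed shift b | p = 30% | p = 50% | p = 70% |
|---|---|---|---|
| 2 points | bias 0.6, error 0.028 | 1.0, 0.032 | 1.4, 0.039 |
| 5 points | 1.5, 0.041 | 2.5, 0.072 | 3.5, 0.123 |
| 10 points | 3.0, 0.095 | 5.0, 0.243 | 7.0, 0.468 |

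The nominal level is 0.025. The last row assumes a rating shift as large as the whole target effect and is shown only as an outer bound.

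**3. Selection in the deletion analysis.** If DSS scores at follow-up have the same distribution in both arms and relate to the outcome in the same way, deletion changes the population but creates no spurious difference. Bias needs the arm to influence the DSS score, through true cognition or through scoring. As an illustration, a simulation assumed no true effect, 50% proxies in the control arm, a correlation of 0.3 to 0.5 between cognitive impairment and outcome score, and nurses in PECAN homes scoring the DSS 0.1 to 0.5 SD lower. The retained share was then 50% in control against 54 to 69% in the intervention arm. A spurious difference of about 0.3 to 2.1 points appeared, here against PECAN because more impaired residents are kept in that arm. Scoring in the opposite direction would reverse the sign.

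**4. Power of the deletion analysis.** With 16 homes per arm and m self-raters per home, SE = √(2 × 200 × (0.38 + 0.62/m) / 16).

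- Normal approximation: 80% at m = 15; 78%, 76% and 70% at m = 10.5, 7.5 and 4.5 (30, 50 and 70% removed).
- t distribution with 30 degrees of freedom: 76% at m = 15, 73% at m = 9 and 65% at m = 4.

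On either basis the high ICC dominates, and losing residents within homes costs little.

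**The case against.** The strongest reply is that deletion does what it is meant to do: it asks whether the result depends on nurse ratings. It also removes mixed-rater change scores, because in a change model adjusted for baseline a resident with a deleted proxy value at t0 or t2 has no usable change score. A set defined by baseline DSS brings those switchers back, with nurse ratings at t2. This stands, and it is why the baseline-defined analysis should be added and should not replace the deletion.

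Self-raters are unblinded as well. This also stands: the retained ratings are not free of expectation effects, so nurse proxies are not the only route to a biased rating.

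Three stronger readings are tempting but are not supported:

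- **A reader might infer that the protocol claims fully blinded outcome assessment.** It does not. The Blinding section limits blinding to those who collect and analyse data, and the nurse proxy is named openly. The sentence under Data collection and management is loose and can be read as covering collection only.
- **A reader might infer that trained PECAN facilitators will serve as proxies.** The article is silent on which nurse rates. It leaves data-collection instructions to standard operating procedures that are not shown. All nursing staff in PECAN homes receive an information session, so excluding facilitators would in any case leave informed, unblinded raters.
- **A reader might infer that the DSS is taken only at the end.** The last month of the intervention fits t2, and Outcome measures, Table 1 and Further statistical issues all require the DSS at each time point. This is a wording matter.

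Finally, nothing in the document suggests that nurses would score the DSS differently by arm. The selection figures show what could happen, not what is expected.

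**Conclusion.** The point holds in a limited form. Unblinded home nurses rate both primary subscales for residents with DSS of 3 or more, and the only stated check on this uses a set determined after randomisation by the same staff group. That check is partial: disagreement with the main result could reflect rater bias, selection or a different effect in cognitively intact residents, and agreement would not settle the matter either. It would go too far to say that rater bias goes untested.

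The size cannot be derived from the protocol. With assumed proxy shares of 30 to 70%, a 2-point shift is almost harmless (per-subscale error about 0.03 to 0.04), while a 5-point shift matters (about 0.04 to 0.12). Power is not a reason to object to the deletion analysis. Because pre-randomisation DSS is already collected, a better-protected analysis is available cheaply. This is a worthwhile improvement to the sensitivity analyses and does not invalidate the primary analysis.

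**What to change.** 1. Keep the deletion analysis, and label it a non-randomised, partial check on dependence on proxy ratings.
2. Add a sensitivity analysis in residents with DSS below 3 at t0, keeping them whatever their later DSS. In the full set, add an arm-by-baseline-DSS-category interaction (below 3 against 3 or more).
3. Report by arm, at t1 and t2, the share of proxy ratings and the number of residents whose rater type changed since baseline.
4. Under Data collection and management, state that blinding covers the collection of data and not the self- or proxy-rating itself.

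The cost is analysis wording, one interaction term and one table; no new assessments are needed. The trade-off is that the baseline-defined set still holds nurse ratings from residents who later cross the cut-off. It protects randomisation but does not fully isolate rater bias. An interaction could likewise reflect either the rater or a real difference in effect. The analyses should therefore be read together, with the switch table showing how much mixing of raters remains.

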### Participants and recruitment

#### Sample size calculation

The study uses a composite primary outcome with two components. To avoid a false positive outcome rate above 5% (significance level), we apply a Bonferroni correction on each of the two components and choose the component-wise significance level as 2.5% (0.05/2 = 0.025). Based on the data from a pilot study, we consider both components as distributional comparable, assuming that both have the same variability. Therefore, the sample size considerations for each component follow the same arguments. Thus, it is sufficient to compute an explicit sample size for one component.

Using the experience of the pilot study (publication in preparation), recruitment of 15 to 20 individuals per cluster is feasible. Thus, the sample size calculation assumed a fixed cluster size of 15 individuals and a free number of clusters. Using pilot data, the intraclass correlation coefficient was estimated at 0.38. This resulted in an inflation factor of (1 + (15 – 1) × 0.38) = 6.32. The subscale variance observed in the pilot study was about 200 (standard deviation 14.14); the effect difference for the participation subscale between the standard and intervention groups was assumed to be 10 at t_2_. The size of one group in this c-RCT is *n* = 241 (38 × 6.32) if the test is two-sided on a significance level of 2.5% and with a power of 80%. This results in a total of 16 clusters per study group (241 / 15 = 16.1). To compensate for individuals terminating the study early due to death or moving, 15% more individuals will be included in the study, resulting in 30 clusters with a cluster size of 18 individuals and two clusters with 19 individuals, the total study size being 578 individuals.

Current experience shows that a few clusters will possibly fail to recruit the necessary number of participants. In this case, we will recruit more participants in other clusters to compensate for this. To maintain the statistical power of the study, the following rule will be applied: number of participants to be additionally recruited in other clusters = 1.5 × number of participants that some clusters fail to recruit.

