#### Randomisation and allocation

Randomisation will be performed using stratified blocks. To ensure the intervention groups are balanced with respect to the location of the nursing homes, block randomisation will be performed taking two strata into account: (1) Halle (Saale) and (2) Rosenheim. Selection bias can be a problem in c-RCTs if participants are recruited after a cluster allocation has been implemented. Therefore, all clusters and participants will be recruited and assessed prior to randomisation. The clusters will be randomised by independent biostatisticians responsible for biometric supervision (UM and LL). Generating, operating and controlling the randomisation will follow the standard operating procedures of the biostatisticians’ institution and will be carried out by professionals who are not involved in trial activities at the nursing homes. Each of the nursing homes will be informed about its intervention allocation by fax by an independent data manager. Subsequently, the data manager will inform the study centres in Halle (Saale) and Rosenheim via fax about the allocation.

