### Statistical analysis

The primary outcomes are the nursing home residents’ participation and activity, measured with the subscales of the ICF-based PaArticular Scales [17]. The evaluation of the impact of joint contractures and the effect of PECAN will be based on an intention-to-treat approach with a significance level of 0.05, which results in a Bonferroni-adjusted significance level of 0.025 for a single test. The analyses will use a generalised linear mixed-effect regression model to compare changes in the scale between the treatment groups over a year. Each nursing home will be given a random intercept. The analysis will be adjusted by the individual baseline values.

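### Comparing complete-case with multiple-imputation results does not test departures from missing at random, so agreement between them would not show that loss to follow-up is harmless

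*Protocol article*

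**What the plan says.** Under Further statistical issues, the protocol article states: "The impact of missing values will be done by comparing complete case analyses with multiple imputation analyses". It does not list the imputation variables. The other sensitivity analysis in that section, "Sensitivity will be ascertained by removing these proxy ratings from the analysis", concerns who rated the outcome and not missing values.

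The Statistical analysis section describes the primary analysis: "The analyses will use a generalised linear mixed-effect regression model to compare changes in the scale between the treatment groups over a year", with a random intercept for each home. It adds: "The analysis will be adjusted by the individual baseline values". The approach is intention-to-treat, and each of the two subscales is tested at 0.025.

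Two further statements bear on what will be missing. The sample size section says: "To compensate for individuals terminating the study early due to death or moving, 15% more individuals will be included in the study". The randomisation section says: "all clusters and participants will be recruited and assessed prior to randomisation". Outcomes are also measured at 6 months (t1), between baseline (t0) and 12 months (t2).

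**The concern.** Because baseline is complete before allocation, the loss that the sample size allows for falls on follow-up scores, chiefly t2. The stated causes are death and moving, in a frail population. It is plausible, though the article does not say so, that some leavers declined more than their observed data would predict.

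Both analyses in the comparison assume that, given the variables they use, leavers resemble stayers. When only the outcome is missing and the imputation draws on the variables already in the analysis model, imputation adds essentially no information and reproduces the complete-case estimate. A richer imputation can correct for loss explained by the extra variables, but still not for loss tied to the unseen remainder of t2. The gap between the two results is thus an incomplete measure of the impact of missing values. A small gap could lend unearned confidence to a primary result close to the significance limit.

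**Working it through.** **1. The plan's own figures.** Inputs from the sample size section: variance 200, difference 10, two-sided level 0.025, power 80%, ICC 0.38, cluster size 15.
- Residents per arm before clustering: 2 × 200 × (2.241 + 0.842)² / 10² = 38.02 (plan: 38).
- Inflation factor: 1 + 14 × 0.38 = 6.32; 38 × 6.32 = 240.2, rounded up to 241; 241 / 15 = 16.1 clusters per arm.
- Total recruited: 30 × 18 + 2 × 19 = 578.

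These reproduce the plan.

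**2. What the comparison can and cannot show.** The article gives no figure for this, so it was simulated: 32 homes of 18 residents, total variance 200, ICC 0.38, a random-intercept model for change adjusted for baseline, 150 trials per scenario, and 10 imputations done by arm with home effects. Assumptions not in the documents: within-home correlations of 0.7 (t0–t1), 0.6 (t0–t2) and 0.75 (t1–t2), and logistic missingness with log odds of 1 per SD. Only t2 was set missing, so every leaver had a t1 score, which favours the comparison. Realised loss was 15–19% at nominal 15% and 30–33% at nominal 30%.

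Bias against the full-data estimate, true effect 0, nominal 15% loss (30% in brackets). Lower scores are better, so a negative bias flatters the intervention. CC = complete case; MI = multiple imputation; gap = absolute difference between CC and MI.

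| Loss depends on | CC bias | MI, baseline only: bias | gap | MI with t1: bias | gap |
|---|---|---|---|---|---|
| t1, opposite directions by arm | −1.09 (−1.98) | −1.01 (−1.80) | 0.09 (0.18) | 0.02 (−0.03) | 1.12 (1.96) |
| t2 itself, opposite directions by arm | −2.07 (−3.61) | −1.96 (−3.40) | 0.11 (0.21) | −1.31 (−2.25) | 0.76 (1.37) |
| part of t2 not predicted by t1, opposite directions by arm | −2.10 (−3.62) | −2.14 (−3.67) | 0.05 (0.05) | −2.33 (−3.98) | 0.24 (0.36) |
| t2 itself, same direction in both arms | 0.06 (−0.04) | 0.05 (−0.01) | 0.01 (0.03) | 0.02 (0.01) | 0.04 (0.05) |

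With loss at random or dependent on baseline only, every bias was at most 0.05. With a true effect of 10 points the pattern was the same: in the third scenario CC was biased by −2.21 (−3.68) and MI with t1 by −2.42 (−4.07), a gap of 0.20 (0.39).

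Three readings follow.
- With baseline only in the imputation, the gap never exceeded about 0.2 points, whatever the bias.
- With t1 included, the comparison exposed t1-dependent loss and removed its bias. It exposed and corrected part of the bias when loss depended on t2 itself.
- For loss tied to the part of t2 that t1 does not predict, the gap stayed below 0.4 points while both analyses were off by about 2 to 4.

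**3. When it would change a conclusion.** The planning standard error is 10 / (2.241 + 0.842) = 10 / 3.083 = 3.24, and the critical difference is 2.241 × 3.24 ≈ 7.27. If a fraction 0.15 of one arm is missing and its true scores are d points worse than imputed, the estimated benefit falls by about 0.15 × d. Significance is lost when d reaches:
- benefit 8.3: (8.3 − 7.27) / 0.15 ≈ 7 points;
- benefit 8.5: (8.5 − 7.27) / 0.15 ≈ 8 points;
- benefit 10: (10 − 7.27) / 0.15 ≈ 18 points (about 9 at 30% loss).

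Half the stated SD is 14.14 / 2 = 7.07 points.

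**The case against.** The strongest objection is that the comparison is not empty. Complete case needs loss unrelated to t2 given the analysis variables; imputation needs this only given everything in its own model. The article collects both subscales, cognition, behaviour, falls, restraints and grade of care at 6 months, and nothing stops the imputation from using them. When it uses t1, the comparison detects t1-dependent loss with a gap of 1.1 to 2.0 points. The section also speaks of missing values generally, and for missing items or covariates imputation does add information. All of this stands. A reader might infer that the two analyses share one assumption, agree by construction, or would signal robustness whatever the loss does. The documents do not support that, because they do not restrict the imputation to the analysis variables.

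It can also be said that the article never promises to treat agreement as robustness, that moving need not be health-related, and that similar loss in both arms largely cancels. These points are fair. The fourth scenario shows the cancelling when there is no true effect; with a true 10-point effect, such loss slightly understated the benefit (complete-case bias 0.42 at nominal 15% loss, 0.66 at 30%).

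Finally, imputation details and further sensitivity analyses commonly sit in a statistical analysis plan, which is not at hand. That bars any complaint about what is left out, and this may not be the trial's only missing-data check. It does not answer the point, which concerns a method the article does state and the purpose it gives that method.

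**Conclusion.** The point holds in this limited form. The stated comparison does not test departures from missing at random, and how much it can show depends on imputation variables that the article does not name. Agreement between the two analyses should not be taken as evidence that about 15% loss is harmless.

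The practical size depends on the result. A benefit near the planned 10 points is fairly safe at 15% loss, since about an 18-point shift in one arm would be needed. A benefit of 8.3 to 8.5 points could be overturned by a shift of about half an SD in one arm's leavers, and the stated check could miss it. These tipping points assume the planning standard error without gain from baseline adjustment, loss of 15%, a shift in one arm only, and no change in the standard error from the shift. The simulated biases rest on the correlations and missingness strengths listed with them. The change is worth making; the point does not invalidate the primary analysis.

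**What to change.** Keep the comparison and specify the imputation: arm, baseline score, t1 score where available, and home. Add a delta-adjusted (pattern-mixture) multiple imputation that shifts imputed t2 scores separately by arm over a stated range, for example 0 to 14 points (about one SD), extended if no crossing occurs. For each of the two primary subscales, report the shift at which the result crosses 0.025.

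Report residents who died separately from those alive with a missing t2 score, and state how each group enters the analysis, so that the shift does not silently assign scores to the dead. If the statistical analysis plan already contains such an analysis, align the two documents.

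The cost is a little extra analysis and one table, with no new data. It should be fixed before the allocation is unblinded to the analysts.
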